### Intervention

2.7

All acupuncture treatments will be administered by licensed acupuncturists with a minimum of 2 years of clinical experience who have completed standardized protocol training. Treatment will commence within 2–4 days of the onset of a spontaneous menstrual period following enrollment. The intervention lasts for 12 weeks, with sessions administered three times per week (every other day), totaling 36 sessions.

#### Manual acupuncture group

2.7.1

The Manual Acupuncture (MA) group will receive treatment using sterile, single-use stainless steel needles (Hwato brand; 0.25 mm diameter needles in 25 mm or 40 mm lengths, and 0.30 mm diameter needles in 75 mm length). The details of acupoint locations and needling techniques are presented in **Table 2**. Treatment alternates between two fixed acupoint sets, commencing with Set A. Set A (supine position) comprises CV12 (Zhongwan), KI16 (Huangshu), CV4 (Guanyuan), KI12 (Dahe), EX-CA1 (Zigong), ST36 (Zusanli), and SP6 (Sanyinjiao). Set B (prone position) includes BL23 (Shenshu), BL33 (Zhongliao), and KI3 (Taixi). Based on the participant’s baseline TCM pattern diagnosis, which is categorized into four distinct patterns, two adjunct points will be added per session according to the following predefined protocol: (1) Kidney Deficiency Pattern: KI6 (Zhaohai) and LR3 (Taichong) (supine); GV4 (Mingmen) and BL18 (Ganshu) (prone); (2) Phlegm-Dampness Pattern: ST40 (Fenglong) and SP9 (Yinlingquan) (supine); BL20 (Pishu) and BL21 (Weishu) (prone); (3) Blood Stasis Pattern: LI4 (Hegu) and SP10 (Xuehai) (supine); BL15 (Xinshu) and BL17 (Geshu) (prone); (4) Liver Qi Stagnation Pattern: LR5 (Ligou) and LR3 (Taichong) (supine); BL18 (Ganshu) and BL19 (Danshu) (prone).

With the patient in an appropriate position, the local skin will be routinely disinfected. BL33 (Zhongliao) is inserted obliquely inferioromedially to a depth of 2.0-2.5 cun to target the third posterior sacral foramen. All other acupoints will be perpendicularly inserted to a standard depth of 1.0-1.2 cun. All needles will be manually manipulated to elicit the characteristic de qi sensation (a composite sensation of soreness, numbness, distension, or heaviness at the acupoint). All acupoint areas are disinfected with 75% alcohol swabs before needling. Needles will be retained for 20 minutes.

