### Traditional Chinese medicine pattern differentiation criteria

2.5

TCM pattern differentiation will be performed by the treating acupuncturist after randomization but prior to the first treatment session. The acupuncturists performing the differentiation are not involved in the randomization process. The diagnostic criteria were developed in accordance with the Criteria of diagnosis and therapeutic effect of gynaenecologic diseases and syndromes in traditional Chinese medicine (ZY/T 001.3-1994) (27) and the General revision and development principle for specification of diagnosis and therapeutic effect evaluation of diseases and syndromes in traditional Chinese medicine (ZY/T 10-2024) (28). Four patterns are predefined: Kidney Deficiency, Phlegm-Dampness, Blood Stasis, and Liver Qi Stagnation. Based on the most prominent clinical presentation, each participant will be assigned to one predominant pattern, with supplementary acupoints added correspondingly as detailed in **Table 2**. Detailed diagnostic criteria are provided in **Supplementary Table 1**.

**Table 2 T2:** Intervention protocol for MA group.

Group & component	Acupoint name (code)	Location (based on WHO standard)	Needling details
A. Core prescription (fixed, alternated by session)			
Set A (Supine)	Zhongwan (CV12)	On the anterior midline, 4 cun superior to the umbilicus.	Perpendicular insertion, 0.5–1.0 cun.
	Huangshu (KI16)	0.5 cun lateral to the umbilicus.	Perpendicular insertion, 0.5–1.0 cun.
	Guanyuan (CV4)	On the anterior midline, 3 cun inferior to the umbilicus.	Perpendicular insertion, 0.5–1.0 cun.
	Dahe (KI12)	0.5 cun lateral to CV4 (Guanyuan).	Perpendicular insertion, 0.5–1.0 cun.
	Zigong (EX-CA1)	3 cun lateral to the midline, 1 cun inferior to CV4.	Perpendicular insertion, 0.5–1.0 cun.
	Zusanli (ST36)	3 cun below ST35, one finger-breadth lateral to tibial crest.	Perpendicular insertion, 0.5–1.2 cun.
	Sanyinjiao (SP6)	3 cun directly above the medial malleolus.	Perpendicular insertion, 0.5–1.0 cun.
Set B (Prone)	Shenshu (BL23)	1.5 cun lateral to the lower border of the L2 spinous process.	Perpendicular insertion, 0.5–1.0 cun.
	Zhongliao (BL33)	In the third posterior sacral foramen.	Oblique insertion toward the foramen, 1.5–2.0 cun.
	Taixi (KI3)	Between the medial malleolus tip and Achilles tendon.	Perpendicular insertion, 0.3–0.5 cun.
B. Standardized adjunct points (added per TCM pattern)			

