Kidney Deficiency	Supine: Zhaohai (KI6), Taichong (LR3)	KI6: In depression inferior to medial malleolus. LR3: On dorsum of foot, between 1st and 2nd metatarsals.	Perpendicular insertion, 0.3–0.5 cun.
	Prone: Mingmen (GV4), Ganshu (BL18)	GV4: Below spinous process of L2. BL18: 1.5 cun lateral to lower border of T9 spinous process.	Perpendicular insertion, 0.5–0.8 cun.
Phlegm-Dampness	Supine: Fenglong (ST40), Yinlingquan (SP9)	ST40: 8 cun superior to lateral malleolus, 2 finger-breadth lateral to tibia. SP9: In depression inferior to medial condyle of tibia.	Perpendicular insertion, 0.5–1.2 cun.
	Prone: Pishu (BL20), Weishu (BL21)	BL20: 1.5 cun lateral to lower border of T11 spine. BL21: 1.5 cun lateral to lower border of T12 spine.	Perpendicular insertion, 0.5–0.8 cun.
Blood Stasis	Supine: Hegu (LI4), Xuehai (SP10)	LI4: On dorsum of hand, between 1st and 2nd metacarpals. SP10: 2 cun above medial border of patella.	Perpendicular insertion, 0.5–0.8 cun.
	Prone: Xinshu (BL15), Geshu (BL17)	BL15: 1.5 cun lateral to lower border of T5 spine. BL17: 1.5 cun lateral to lower border of T7 spine.	Perpendicular insertion, 0.5–0.8 cun.
Liver Qi Stagnation	Supine: Ligou (LR5), Taichong (LR3)	LR5: 5 cun above medial malleolus, on posterior border of tibia. LR3: On dorsum of foot, between 1st and 2nd metatarsals.	Perpendicular insertion, 0.5–0.8 cun.
	Prone: Ganshu (BL18), Danshu (BL19)	BL18: 1.5 cun lateral to lower border of T9 spine. BL19: 1.5 cun lateral to lower border of T10 spine.	Perpendicular insertion, 0.5–0.8 cun.

To ensure the reproducibility of TCM pattern differentiation, all acupuncturists will undergo a 2-day centralized training workshop covering the diagnostic criteria for the four predefined patterns, followed by a certification examination (≥80% accuracy required).

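### The needle depths in Section 2.7.1 disagree with Table 2 at most acupoints, and nothing says which source prevails

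*Protocol article*

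**What the plan says.** Depth in the manual acupuncture arm is stated in two places in the protocol article.

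- **Section 2.7.1 (text).** One point is singled out: "BL33 (Zhongliao) is inserted obliquely inferioromedially to a depth of 2.0-2.5 cun". For the rest there is a single rule: "All other acupoints will be perpendicularly inserted to a standard depth of 1.0-1.2 cun". The section also refers to Table 2 for locations and needling technique.
- **Table 2 (in Section 2.5).** Depth is given row by row. BL33: "Oblique insertion toward the foramen, 1.5–2.0 cun". Seven core points (CV12, KI16, CV4, KI12, EX-CA1, SP6, BL23): "Perpendicular insertion, 0.5–1.0 cun". ST36, ST40 and SP9: "Perpendicular insertion, 0.5–1.2 cun". KI3, and KI6 with LR3 under Kidney Deficiency: "Perpendicular insertion, 0.3–0.5 cun". The remaining adjunct entries, including every prone adjunct point: "Perpendicular insertion, 0.5–0.8 cun".

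The article does not say whether text or table governs where they differ.

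**The concern.** The text rule is unqualified: it covers every point other than BL33 and calls its range a standard. The table is equally definite and is the source that the text itself cites. An acupuncturist cannot follow both at most points.

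Three things depend on this.

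- **What is being tested.** Section 2.7.2 explains that the sham is meant to limit specific effects partly by needling shallowly. Depth is thus part of the contrast between arms, and the active side of it has two specifications.
- **Fidelity.** Section 2.11 relies on an independent expert who checks recorded sessions. At a point where the ranges do not overlap, a needle that passes against the table fails against the text, and the reverse.
- **The per-protocol set.** Section 2.13 excludes participants with major protocol violations. If depth deviations were classed that way, membership would depend on the source used.

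Several of the points in conflict lie on the back, so a safety question also arises.

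**Working it through.** **Method.** Each Table 2 range was set against the text range: 2.0–2.5 cun for BL33 and 1.0–1.2 cun for every other point. Each pair was classed as no overlap (table maximum below text minimum), one shared end value, or text range inside table range. Table 2 has 10 core and 16 adjunct entries, 26 in all. LR3 and BL18 each appear under two patterns, which leaves 26 − 2 = 24 distinct points.

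| Table 2 entries | Table (cun) | Text (cun) | Result | Entries |
|---|---|---|---|---|
| KI3; KI6 and LR3 (Kidney Deficiency) | 0.3–0.5 | 1.0–1.2 | no overlap, gap 1.0 − 0.5 = 0.5 | 3 |
| GV4, BL15, BL17, BL18 (two entries), BL19, BL20, BL21, LI4, SP10, LR5, LR3 (Liver Qi Stagnation) | 0.5–0.8 | 1.0–1.2 | no overlap, gap 1.0 − 0.8 = 0.2 | 12 |
| CV12, KI16, CV4, KI12, EX-CA1, SP6, BL23 | 0.5–1.0 | 1.0–1.2 | meet at 1.0 only | 7 |
| BL33 | 1.5–2.0 | 2.0–2.5 | meet at 2.0 only | 1 |
| ST36, ST40, SP9 | 0.5–1.2 | 1.0–1.2 | text inside table | 3 |

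**Totals.**

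- No overlap: 3 + 12 = 15 of 26 entries, made up of KI3 and 14 of the 16 adjunct entries. Removing the repeats of LR3 and BL18 gives 15 − 2 = 13 of 24 distinct points, or 54%.
- One shared value: 7 + 1 = 8.
- Compatible across a range: 3.
- Check: 15 + 8 + 3 = 26. No entry has the same range in both places.
- Distinct points with no overlap or a single shared value: 13 + 8 = 21 of 24.

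**Back and sacral points.** There are nine: GV4, BL15, BL17, BL18, BL19, BL20, BL21, BL23 and BL33. The first seven do not overlap the text; BL23 and BL33 share one value.

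**Largest relative difference.** At KI3, KI6 and LR3 under Kidney Deficiency, the text minimum is 1.0/0.5 = 2 times the table maximum.

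**Reach.** Sessions alternate between the two sets, starting with Set A, over 36 sessions, so 36/2 = 18 are Set B. A Set B session uses BL23, BL33, KI3 and two prone adjunct points, five in all. KI3 and both adjuncts fall in the no-overlap group under all four patterns. In half of the scheduled sessions, therefore, three of five points cannot meet both sources, whatever the participant's pattern.

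**The case against.** The strongest reply is that the text sentence is a loose summary, that Table 2 is the working specification because Section 2.7.1 points to it, and that centralized training will teach one version. It is also fair to say that on the strict no-overlap test the majority is narrow (13 of 24), and that different practice between centers is possible but not shown.

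Part of this stands: nothing shows that centers will in fact diverge. But the article never says that the table governs, and the text rule is worded as an instruction. Training has to teach one figure, and the protocol supplies two. The certification test described under Table 2 concerns pattern differentiation. Condensing a protocol into an article can explain missing detail, but not two incompatible figures.

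A reader might also infer more than the article supports:

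- **That the contradiction is a demonstrated hazard.** The article gives no risk by depth and no depth limit. Concern at the back points is plausible, but its size cannot be stated.
- **That per-protocol status is already undefined.** Section 2.13 defines it by completing 12 weeks, receiving at least 80% of sessions and having no major violation. The first two do not depend on depth, and no section makes a depth deviation a major violation.
- **That lack of blinding at the sites makes it worse.** Section 2.6 leaves only the acupuncturists unblinded, and blinding does not bear on which depth is used.
- **That LR3's two table depths are a further error.** They sit under different patterns, each participant is assigned one predominant pattern, and the ranges meet at 0.5 cun. They may be intended.
- **That the primary analysis or sample size is wrong as a result.** Depth enters neither. The planned 62 per group gives 62/(1 − 0.20) = 77.5, rounded up to 78, as stated.

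**Conclusion.** The contradiction is real. Text and table do not overlap for 15 of 26 entries (13 of 24 distinct points), and they share only one end value for eight more. Only ST36, ST40 and SP9 can meet both sources across a range. Acupuncturists at six centers could give different active treatments and each comply with one source, and the fidelity checks have no single depth standard.

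The conclusion rests on reading both sources as instructions, which their wording supports, and on the absence of any rule of precedence. The per-protocol consequence is conditional on how major violations are defined. The safety concern is plausible and unquantified. The defect lies in the specification of the intervention, not in the endpoint, the sample size or the analysis model.

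**What to change.** The responsible clinical lead should reconcile Section 2.7.1 with Table 2 so that text and table agree for every point, BL33 included. The simplest form is to let the text refer to the table without restating depths. The lead should also confirm whether LR3 is meant to have different depths under Kidney Deficiency and Liver Qi Stagnation, and say so if it is. The reconciled table should then be named as the single reference for acupuncturist training and for the recorded-session fidelity checks, with a statement of whether a depth deviation can count as a major protocol violation.

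Which depth is right is a clinical decision, and this review takes no position on it.

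The cost is a protocol correction and a notice to six centers. Sample size, endpoint and analysis model are unchanged. If treatment has already begun, each center should also record which source it has been following.

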#### Sham acupuncture group

2.7.2

The Sham Acupuncture (SA) group will receive treatment at predefined non-acupoint (NA) locations using sterile, single-use stainless steel needles (Hwato brand; 0.25 mm diameter, 25 mm length). The locations of these sham points, which are near but distinct from conventional acupoints, are specified in **Table 3** (e.g., 1 cun lateral to CV4).

**Table 3 T3:** Intervention protocol for SA group.

Component	Acupoint / sham point name	Location	Needling details
Set A (Supine)	NA-1	1.0 cun lateral to the left of CV12.	Needle: Φ0.25×25 mm sterile needle. Depth: Superficial insertion of 2–3 mm.
	NA-2	1.0 cun lateral to KI16.	Same as above.
	NA-3	1.0 cun lateral to the right of CV4.	Same as above.
	NA-4	1.0 cun lateral to KI12.	Same as above.
	NA-5	10 mm lateral to ST36.	Same as above.
	NA-6	Midpoint between SP6 and the medial border of Achilles tendon.	Same as above.
Set B (Prone)	NA-7	Midpoint between BL23 and the inner line of Bladder Meridian (approx. 0.75 cun lateral).	Same as above.
	NA-8	1.0 cun lateral to BL33.	Same as above.
	NA-9	Anterior border of Achilles tendon, level with KI3.	Same as above.

Treatment will alternate between two standardized sets of sham points per session, starting with Set A (supine position), which comprises non-acupoints near CV12 (NA-1), KI16 (NA-2), CV4 (NA-3), KI12 and EX-CA1 (NA-4), ST36 (NA-5), and SP6 (NA-6). Set B (prone position) includes non-acupoints near BL23 (NA-7), BL33 (NA-8), and KI3 (NA-9). No pattern-based adjunct points will be applied.

With the patient in a suitable position, the skin at each sham point will be routinely disinfected. All sham points receive identical alcohol disinfection before needling. A needle will be inserted superficially to a depth of 2–3 mm. No needle manipulation will be performed, and no de qi sensation will be sought or elicited. The needle will be retained for 20 minutes.

Non-acupoint shallow needling was selected as the sham control to provide a credible blinding experience without specialized devices, while minimizing specific therapeutic effects by avoiding de qi and deep insertion. To minimize unblinding risk, the insertion depth (2–3 mm) and needle type were standardized across all sham sessions. All participants are informed that “acupuncture sensations may vary from person to person” to reduce expectation bias.

### Concomitant medication

2.8

To ensure patient safety and standardize clinical management during the trial, the use of concomitant medication will be permitted and recorded under the following specific circumstances:

Rescue Medication for Prolonged Amenorrhea: If a participant experiences amenorrhea for more than 90 days during the trial period, oral dydrogesterone (10 mg, once daily for 10 days) may be administered to induce withdrawal bleeding. All rescue interventions will be thoroughly documented within the designated rescue medication section of the case report form (CRF).Pre-existing chronic medications unrelated to gynecology or fertility management (e.g., agents for hypertension, hypothyroidism) may be continued throughout the trial, provided the site investigator confirms no interference with trial outcome evaluation. Full details of all concurrent medications—including drug name, dosage, administration frequency, and clinical indication—must be recorded comprehensively in the Concomitant Medication module of each participant’s case report form (CRF).

### Outcome measurement

2.9

All outcome measurements will be scheduled according to the study timeline (**Table 1**). Baseline assessments will be performed before randomization and prior to the first treatment. Primary and secondary outcomes are assessed at the end of the 12-week treatment period (Week 12) and at the end of the 12-week follow-up period (Week 24).

#### Primary outcome

2.9.1

The primary outcome is the cycle ovulation rate (COR). To account for the inherent irregularity of menstrual cycles in PCOS, the 12-week treatment period is divided into three standardized 28-day (4-week) time windows (i.e., Weeks 1-4, 5-8, and 9-12), each serving as an observation unit for detecting ovulation. COR is calculated using the following formula: COR (%) = (Number of 28-day time windows with ultrasound-confirmed ovulation/Number of completed full 28-day time windows) × 100% (19, 20). For participants who complete the full 12-week treatment period, the denominator is 3. For participants who withdraw early, the denominator is the number of full 28-day time windows completed before withdrawal. Participants who complete at least one full 28-day time window will be included in the primary analysis. Ovulation is confirmed by transvaginal ultrasound (TVUS), which serves as the gold standard. A window is considered ovulatory when TVUS documents the development of a dominant follicle (≥18 mm in diameter) followed by its subsequent collapse or disappearance, accompanied by the appearance of free fluid in the pouch of Douglas (29). Given that women with PCOS often have prolonged and irregular menstrual cycles, urinary LH test strips will be used daily to optimize the timing of ovulation monitoring. For each menstrual cycle, testing will begin on day 10–12 of that cycle and continue until ovulation is confirmed or the cycle ends. Once a positive LH test is observed, transvaginal ultrasound will be performed to confirm follicular rupture and ovulation. For participants who do not achieve a positive LH test, daily LH test strip use will continue until the end of that menstrual cycle. Daily basal body temperature (BBT) charting will be maintained as a supplementary record.

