### Randomization, allocation and blinding

2.6

Eligible participants will be randomly assigned at a 1:1 ratio to either the manual acupuncture (MA) group or the sham acupuncture (SA) group. Randomization will be stratified by the six participating clinical centers to ensure baseline balance across groups. An independent statistician will generate the randomization sequence using SAS software (version 9.4), with randomly permuted block sizes of 2 and 4. This sequence will be implemented and managed through a centralized, web-based randomization system maintained by an independent clinical research organization (CRO), ensuring allocation concealment. After obtaining written informed consent and confirming final eligibility, the site investigator will access the central system. The system will then automatically assign a unique trial identifier and the corresponding treatment allocation (MA or SA). The allocation remains fully concealed from both the investigator and the participant until the moment of assignment, thereby preventing selection bias. Owing to the nature of the interventions, the acupuncturists administering the treatments cannot be blinded. Therefore, this is an assessor- and participant-blinded trial. All efforts will be made to maintain blinding of the participants, outcome assessors, and data analysts throughout the study.

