### Sample size

2.12

The sample size calculation was based on the primary outcome, the cycle ovulation rate (COR). Based on a systematic review of prior studies (15, 19, 20) and our pilot data[Trial Registration Number: ChiCTR2300073494], we anticipated a COR of 65% in the MA group and 40% in the SA group at the end of the treatment. Using a two-sided Chi-square test with a significance level (α) of 0.05 and a power (1-β) of 80%, the required sample size per group was calculated to be 62 participants. Accounting for an estimated 20% dropout rate over the 24-week study period, the final target sample size was 78 participants per group, for a total of 156 participants. This calculation was performed using PASS software (version 15.0).

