### Statistical analysis

2.13

All analyses will adhere to the Intention-to-Treat (ITT) principle. The baseline characteristics will be summarized descriptively by group using means (standard deviations) or medians (interquartile ranges) for continuous variables and frequencies (percentages) for categorical variables to assess between-group comparability.

For the primary outcome, the cycle ovulation rate (COR) at Week 12, any missing data will be handled using multiple imputation by chained equations (MICE) with 20 imputed datasets, and results combined using Rubin’s rules (35). The COR will be compared between groups using a linear mixed-effects model with study center as a random effect. The result will be presented as the mean difference between groups with its 95% confidence interval. As a sensitivity analysis, a per-protocol (PP) analysis will be performed, including only participants who completed the 12-week intervention with adequate adherence (defined as receiving ≥80% of the scheduled acupuncture sessions) and without major protocol violations.

To assess the sustainability of the treatment effect, the COR at Week 12 and Week 24 will be analyzed together using a linear mixed-effects model for repeated measures, including group, time point (Week 12, Week 24), and group-by-time interaction as fixed effects, with study center and participant as random effects (36).

The analyses for secondary outcomes will be conducted using available data. Continuous outcomes will be analyzed using Analysis of Covariance (ANCOVA), adjusting for corresponding baseline values and study center (37). Binary outcomes will be analyzed using generalized linear mixed models, incorporating study center as a random effect (38). All statistical tests will be two-sided, and a p-value < 0.05 will be considered statistically significant. All analyses will be performed using SAS software (version 9.4, SAS Institute Inc., Cary, NC, USA).

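### The completed-window rule for the primary outcome contradicts the promised intention-to-treat analysis and leaves the planned multiple imputation no withdrawal to act on

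*Protocol article*

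**What the plan says.** Protocol article, section 2.9.1 (Primary outcome), splits the 12 treatment weeks into three four-week windows. COR is the share of completed windows with ultrasound-confirmed ovulation. A woman who finishes treatment is scored on three windows; for one who leaves early, "the denominator is the number of full 28-day time windows completed before withdrawal". The analysis set follows: "Participants who complete at least one full 28-day time window will be included in the primary analysis".

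Section 2.13 (Statistical analysis) says "All analyses will adhere to the Intention-to-Treat (ITT) principle". For the Week 12 COR it adds that "any missing data will be handled using multiple imputation by chained equations (MICE) with 20 imputed datasets". COR is then compared in a linear mixed model with centre as a random effect, with no weight stated for the number of windows. The one sensitivity analysis named for this outcome is per-protocol.

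Section 2.12 (Sample size): "we anticipated a COR of 65% in the MA group and 40% in the SA group at the end of the treatment", and the numbers were raised "Accounting for an estimated 20% dropout rate over the 24-week study period".

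**The concern.** The two sections give different primary analyses. An analyst who follows 2.9.1 drops women with no finished window and imputes nothing for the others who withdrew. One who follows 2.13 keeps all randomised women and imputes. Both could claim to have followed the protocol and still report different primary results. The per-protocol analysis narrows the set further, so it cannot show what the exclusion does.

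The shrinking denominator is a second difficulty. Treatment starts two to four days after the onset of a period (section 2.7), in women whose cycles last 35 to 60 days (section 2.3). The first window therefore covers mainly the early part of a long cycle. A score of 0 or 1 on that window alone measures something different from a three-window rate, and it is noisier. If early withdrawal differs by arm, which is possible when one arm has deeper needling with de qi and the other shallow needling without manipulation, the treatment difference can shift.

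**Working it through.** **1. The plan's own figure.** Inputs from section 2.12: 65% against 40%, two-sided chi-square test, alpha 0.05, power 80%; allocation 1:1 (section 2.6). With pooled variance and no continuity correction, n = [1.960·√(2·0.525·0.475) + 0.842·√(0.65·0.35 + 0.40·0.60)]² / 0.25² = 61.4, so 62 per group. Then 62/0.8 = 77.5, so 78 per group and 156 in all. The stated figures reproduce, and this point does not touch them.

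**2. What is left to impute under section 2.9.1.**

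| Windows finished | Week 12 COR | In primary set? | Value to impute? |
|---|---|---|---|
| 3 | out of 3 | yes | none |
| 2 | out of 2 | yes | none |
| 1 | out of 1 | yes | none |
| 0 | undefined | no | excluded |

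**3. Are the windows alike?** Assumptions: start on cycle day 3, cycle lengths L uniform on the 26 values 35 to 60, luteal phase 14 days, every cycle ovulatory. Ovulation in cycle k then falls on study day kL − 16. The number of lengths with an ovulation in days 1–28, 29–56 and 57–84 is 10, 18 and 14 of 26: 38%, 69% and 54%, mean 53.8%. Starting on day 2 gives 35/69/54%; starting on day 4 gives 42/65/54%.

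**4. Size of the shift.** Scale that shape to the planned means: 46.4/83.6/65.0% (manual acupuncture) and 28.6/51.4/40.0% (sham). The mean of windows 1 and 2 equals the three-window mean, so only leaving after window 1 moves the expected COR, by −18.6 points in the manual arm and −11.4 in the sham arm. With a fraction d0 lost before finishing window 1 and d1 lost after it, an arm's mean falls by d1/(1 − d0) times that gap. The dropout timing is assumed, because the protocol gives none.

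- 20% in both arms (3% with no window, 12% after window 1, 5% after window 2): 0.12/0.97 = 0.124. Manual 65 − 2.3 = 62.7; sham 40 − 1.4 = 38.6; difference 24.1.
- 10% in both arms, same relative timing: 0.06/0.985 = 0.061; 63.9 − 39.3 = 24.6. Spread evenly over the three points: 24.75.
- 20% manual, 10% sham, same relative timing: 62.7 − 39.3 = 23.4. Reversed: 63.9 − 38.6 = 25.3.

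**5. Dropout linked to ovulation.** This simulation had equal window rates, within-woman correlation 0.3 (assumed) and a true difference of 25 points. Random dropout of about 20% gave 24.9, which is no bias. Dropout linked to anovulation gave 23.6 when confined to the manual arm, 26.4 when confined to the sham arm and 25.1 when similar in both. Ovulating women leaving the manual arm more often gave 25.7. The one-arm anovulation scenarios are severe: 74.5% of the manual arm or 61.8% of the sham arm finish all windows.

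**6. The excluded women.** Suppose x of 78 per arm finish no window (x is assumed) and the rest show 65% and 40%. The extremes for all randomised women are [(78 − x)·0.25 ± x]/78: 18.6 to 28.8 points for x = 4, and 12.2 to 32.7 for x = 8. These are limits, not expectations.

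**7. Noise.** At 65%, a one-window COR has variance 0.65·0.35 = 0.23. A three-window COR has 0.23/3 = 0.08 if windows are independent, or 0.08·(1 + 2·0.3) = 0.12 at correlation 0.3.

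**The case against.** - **Imputation might still act.** A woman who stays 12 weeks but misses ultrasound or test strips has finished windows of unknown status. A reader might infer that imputation can never operate; that goes too far. It could act if such windows counted as missing. Section 2.9.1 does not say so, and the coding may sit in an analysis plan that is not shown. This would not change the handling of withdrawals.
- **Women are still compared as randomised.** This is true, and the set is prespecified, so modified intention-to-treat is the fair name. It is still defined by an event after randomisation, and section 2.13 makes the unqualified claim.
- **Window 1 is not each woman's worst window.** A reader might infer that it is. In the model above, for 10 of the 26 cycle lengths (35 to 44 days) window 1 contains an ovulation while window 2 or 3 does not. Only the average is lowest.
- **The shape model cannot produce the planned rate.** With every cycle ovulatory its mean COR is 53.8%, below 65%. Reaching 65% would need shorter cycles, which would change the shape. Step 4 shows an order of magnitude only.
- **The dropout figure covers 24 weeks.** Losses after Week 12 do not touch the Week 12 COR, so 20% of 156, about 31 women, is a ceiling.

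All five stand as limits on size. None removes the contradiction between the two sections.

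**Conclusion.** The contradiction stands and concerns the primary analysis. For withdrawals, section 2.9.1 leaves nothing to impute, and it replaces the promised intention-to-treat set with a modified one. A COR on one window differs in expectation and precision from a COR on three, and no weighting is stated.

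The bias is modest and its direction is unknown. A 25-point difference becomes about 24 to 25 points with equal dropout of 10% to 20% by Week 12, and 23.4 to 25.3 with 20% against 10% at the same relative timing. These figures rest on assumed dropout timing and on the window shape in step 3.

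A reader might infer shifts as large as 22 to 27 points. Those arise only when one arm loses women before or just after window 1 (5% and 15%) and the other only after window 2 (10%), which gives 22.1, or 26.8 with the arms reversed. Nothing in the protocol predicts such opposite timing, or withdrawal that depends on arm. This should be fixed before the data are analysed, but it does not invalidate the design.

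**What to change.** In sections 2.9.1 and 2.13:

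1. Make all randomised women the primary analysis set.
2. Define COR over three windows for everyone, and treat each unfinished window as a missing yes/no value.
3. Impute these values at window level with the chained equations already planned, by arm, using centre, baseline cycle length and the woman's other windows. Centres average 78/6 = 13 women per arm, so check that the centre terms can be fitted.
4. In each imputed dataset compute COR as the sum of ovulatory windows divided by 3, fit the planned model, and combine by Rubin's rules.
5. Keep the completed-window rule as a sensitivity analysis. Add one that counts missing windows as non-ovulatory, because the imputation assumes missing at random. The latter does not suit the primary role: under the random 20% dropout in step 5 it gives 56.1% against 34.5%, a difference of 21.6 points.
6. State whether a finished window with missed monitoring counts as missing or as non-ovulatory.

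A window-level binary mixed model on all randomised women would be a reasonable alternative, though it would change the planned effect measure.

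The cost is revised wording and some programming, with no new patients or data. The change should be dated before database lock and made without sight of results by arm.
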